## 3. Statistical Considerations

### 3.1. Sample Size and Power

This study’s hypothesis is that the rates of hospitalization (inpatient) will be similar among the NDSD and DS cases. This is a matched set of cases (DS) and controls (NDSD) with two matched controls per case. The second comparison group is the WD group (1:1 matched with case). Based on previous data on the hospitalization rates of shigellosis cases in Mirzapur (obtained via personal communication with [name] et al.), we assume that the probability of hospitalization among the controls will be 20%. Since it is not known, as a general practice, the correlation coefficient for exposure between the matched cases and controls is set to 0.2. If the true odds ratio for hospitalization in the exposed subjects relative to the unexposed subjects is 0.5, we will need to study 123 cases of shigellosis with dysentery with 2 matched controls per case in order to be able to reject the null hypothesis that this odds ratio equals 1 with a probability (power) of 0.8. If the alternative hypothesis is not satisfied, then we will accept the null hypothesis of no difference in hospitalization rates between the cases and controls. The Type I error probability associated with the test of this null hypothesis is 0.05. With an estimated 20% of participants lost to follow-up, we will enroll 148 children each in the DS and WD groups and 296 in the NDSD group (total: 592).

For the RLDT evaluation in the primary healthcare facility, a sample size of 225 (45 subjects with Shigella) achieves 80% power to detect a change in sensitivity from 0.60 to 0.80 using a two-sided binomial test and 100% power to detect a change in specificity from 0.60 to 0.80 using a two-sided binomial test with the target significance level set to 0.05. The actual significance level achieved by the sensitivity test is 0.0336 and that achieved by the specificity test is 0.0397. The prevalence of the disease is ~20%.

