### 3.2. Statistical Analyses

The indicators of severity and symptoms determined by the morbidity indicators, hospitalization, and diarrheal disease score between the cases and controls at baseline (i.e., upon enrolment) will be evaluated using conditional logistic regression adjusting for sex and other confounding factors. The impact of the initial shigellosis or WD episode on the future morbidity, hospitalization, and mortality of the children, during the follow-up period of 12 months for the NDSD and DS groups or 3 months for the WD group, will be analyzed accounting for the confounding factors. Any antibiotic use during the follow-up period will be recorded and considered during analysis. Initially, bivariate conditional logistic regression models will be developed considering each one of the sociodemographic factors for the risk of shigellosis to select the variables for adjustment in the multivariable model.

The Z scores of all anthropometric measurements of the cases and their matched controls at different time intervals will be compared using paired *t*-tests. We will perform linear regression analyses comparing the baseline Z scores and changes in the Z scores from enrolment to the 3- or 12-month follow-up assessment, adjusting for the enrolment Z score, the duration of the follow-up period, sociodemographic covariates, antibiotic use, future diarrhea episodes, and any hospitalization in the follow-up period, using jack-knife estimates of standard error [26].

The same analytic techniques will be used for evaluating the data from the Bayley and WPPSI scales by comparing both the Z scores and age-adjusted composite scores of all developmental domains in the unadjusted model. In the multivariable-adjusted liner regression model, we will adjust specific baseline test scores for each domain and any other related sociodemographic variables that are significantly different between the groups at baseline, significantly different between the children lost to follow up and the tested children, or significantly associated with developmental outcome measures, e.g., socioeconomic status, sex, mother’s education, HOME assessment result, etc. Five behavioral outcomes will be summed up as total scores and will be used in a similar analysis. Sensitivity and mediation analyses will also be conducted using a Structural Equation Model (SEM) [27] to explore the underlying mechanisms or processes influencing the outcomes.

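### Section 3.1 presents 148 matched sets as 123 plus 20% loss, but 148 is 123 × 1.2; it absorbs about 17% loss and leaves about 118 DS cases at 20%

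*Protocol article*

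**What the plan says.** All figures are in section 3.1 of the protocol article.

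- Design: "This is a matched set of cases (DS) and controls (NDSD) with two matched controls per case". The watery diarrhea (WD) group is matched 1:1 to the cases.
- Requirement before loss: "we will need to study 123 cases of shigellosis with dysentery with 2 matched controls per case", for 80% power at a Type I error of 0.05.
- Enrolment after loss: "With an estimated 20% of participants lost to follow-up, we will enroll 148 children each in the DS and WD groups". The non-dysentery (NDSD) number is set at twice that, 296, which makes 592 children overall.

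The section does not give the formula that leads from 123 to 148.

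The hypothesis in 3.1 concerns inpatient hospitalization in NDSD and DS cases, with no time point attached. Section 2.4 lists the need for admission among the features of the index illness, and also has field workers record hospitalizations during follow-up. Section 3.2 has an analysis for each. Severity, symptoms and hospitalization "at baseline (i.e., upon enrolment) will be evaluated using conditional logistic regression". Future hospitalization is analysed separately, over 12 months for NDSD and DS and 3 months for WD.

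**The concern.** An allowance for loss should make the number remaining after loss equal to the number required. That means dividing the requirement by the retained fraction. Multiplying by one plus the loss rate always falls short, because the loss applies to the larger enrolled number. The three figures in 3.1 (123 required, 20% lost, 148 enrolled) therefore do not fit together.

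An allowance for loss to follow-up also makes sense only for an outcome observed during follow-up, whereas 3.2 analyses hospitalization upon enrolment. So the allowance is either unnecessary for the sized test or too small for it, and 3.1 does not say which.

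The stake is modest but real. Section 3.1 says that if the alternative is not supported, the null hypothesis of equal hospitalization rates will be accepted. Under that rule, any loss of power raises the chance of wrongly concluding that there is no difference. The matched comparisons made after enrolment also depend on how many cases remain together with their controls.

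**Working it through.** **Inputs (section 3.1):** 123 sets required, each with 1 DS case and 2 NDSD controls; 20% loss; 148 DS, 148 WD and 296 NDSD enrolled (total 592); power 0.80; Type I error 0.05. Sidedness is not stated for this test, so two-sided is assumed.

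**1. The plan's figure.** 123 × (1 + 0.20) = 147.6, rounded up to 148. This reproduces the stated enrolment; NDSD is 2 × 148 = 296.

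**2. The number that keeps 123.** 123/(1 − 0.20) = 153.75, so 154 DS, 154 WD and 308 NDSD. The total is 616, which is 24 more than 592.

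**3. What 148 provides.**
- Loss absorbed: 1 − 123/148 = 0.169, about 17%.
- DS cases left at 20% loss: 148 × 0.8 = 118.4, about 118 (5 short of 123).
- NDSD controls left: 296 × 0.8 = 236.8, about 237 (against 2 × 123 = 246).

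**4. Matched sets, if children are lost independently at 20% (my assumption).** The 118 already excludes every set whose case is lost. A further set drops out when both of its controls are lost.
- Case and at least one control: 148 × 0.8 × (1 − 0.2²) = 113.7, about 114.
- Of these, complete 1:2 sets: 148 × 0.8³ = 75.8, about 76.
- One control left: 113.7 − 75.8 = 37.9, about 38.

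**5. Power, accepting that 123 full sets give 80%.** The standardized effect at 123 sets is 1.960 + 0.842 = 2.802, and it scales with the square root of the number of sets. Power = Φ(2.802 × √(n/123) − 1.960).

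| Situation | n (in full 1:2 sets) | Scaled effect | Power |
|---|---|---|---|
| Requirement | 123 | 2.802 | 80% |
| 20% of cases lost, remaining sets full | 118 | 2.744 | 78% |
| 114 sets, all full | 114 | 2.697 | 77% |
| 76 full sets + 38 with one control | 76 + 0.75 × 38 = 104.5 | 2.582 | 73% |

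The weight 0.75 comes from the usual efficiency m/(m + 1) of a set with m controls: (1/2)/(2/3) = 0.75.

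**6. If the outcome is admission at enrolment.** It is known for every enrolled child, so all 148 sets count, 25 more than the 123 required.

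**The case against.** The strongest reply is that the sized test is not affected. The 123 was derived for inpatient hospitalization. Section 2.4 treats the need for admission as a feature of the index illness, and 3.2 analyses it upon enrolment by conditional logistic regression. On that reading the requirement is exceeded. This stands, and it is why a shortfall in the sized comparison cannot be asserted outright. It does not rescue the sentence in 3.1, because an allowance for follow-up loss then has no role in that test, and 148 is still not 123 protected against 20% loss.

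A second reply is that the set counts assume too much. This stands in part. Independent loss is not stated in the article. Conditional logistic regression is named for the baseline comparison, while future hospitalization is only said to be analysed with account taken of confounders. Other follow-up analyses use linear regression or unpaired tests. Broken sets clearly matter for the paired t-tests in 3.2, less clearly elsewhere.

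Two stronger readings are tempting and are not supported:

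- A reader might infer that the study falls short of its required number for every follow-up outcome. Section 3.1 sets no required number for growth, development, inflammation or mortality, and a figure built on an odds ratio does not transfer to continuous outcomes.
- A reader who recomputes power from the inputs in 3.1 might blame the loss allowance for a result far below 80%. With the stated inputs the Dupont matched formula (two-sided) gives only about 52% at 123 sets, before any loss. That gap concerns how 123 was obtained. It is a separate question and is not an effect of the loss allowance.

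**Conclusion.** The point holds as an inconsistency in 3.1: 148 is described as covering 20% loss and covers about 17%. At 20% loss about 118 DS cases remain, against 123 required.

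The consequence depends on the outcome sized. For admission at enrolment there is no shortfall. For hospitalization during follow-up, the loss factor costs about 2 points of power (80% to 78%). If follow-up is analysed in matched sets and loss is independent, power is about 77% with 114 full sets and about 73% once sets with one control are given their lower weight.

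These power figures take the plan's equation of 123 sets with 80% power as given and do not vouch for it. The correction is worth making because a stated sample-size figure does not deliver what it is said to deliver. It does not threaten the study.

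**What to change.** Amend the last sentence on sample size in 3.1 in one of two ways:

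- If admission at enrolment is the sized outcome, say so. State that all 148 matched sets contribute, and drop the attrition allowance from the justification.
- If hospitalization during follow-up is the sized outcome, state that 148 allows for about 17% loss, that about 118 DS cases remain at 20% loss, and that power is correspondingly lower (about 78% on the plan's own basis).

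In either case, give the number expected to be retained for the matched follow-up analyses: about 118 cases, and about 114 sets with a case and at least one control if loss is independent at 20%.

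The cost is one or two sentences and a slightly less favourable stated figure. No extra enrolment is needed. Enrolling 154 DS, 154 WD and 308 NDSD (24 more children) would be required only if the sponsor wishes to keep the claim of 123 cases after 20% loss.

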### 3.2. Statistical Analyses

The indicators of severity and symptoms determined by the morbidity indicators, hospitalization, and diarrheal disease score between the cases and controls at baseline (i.e., upon enrolment) will be evaluated using conditional logistic regression adjusting for sex and other confounding factors. The impact of the initial shigellosis or WD episode on the future morbidity, hospitalization, and mortality of the children, during the follow-up period of 12 months for the NDSD and DS groups or 3 months for the WD group, will be analyzed accounting for the confounding factors. Any antibiotic use during the follow-up period will be recorded and considered during analysis. Initially, bivariate conditional logistic regression models will be developed considering each one of the sociodemographic factors for the risk of shigellosis to select the variables for adjustment in the multivariable model.

The Z scores of all anthropometric measurements of the cases and their matched controls at different time intervals will be compared using paired *t*-tests. We will perform linear regression analyses comparing the baseline Z scores and changes in the Z scores from enrolment to the 3- or 12-month follow-up assessment, adjusting for the enrolment Z score, the duration of the follow-up period, sociodemographic covariates, antibiotic use, future diarrhea episodes, and any hospitalization in the follow-up period, using jack-knife estimates of standard error [26].

The same analytic techniques will be used for evaluating the data from the Bayley and WPPSI scales by comparing both the Z scores and age-adjusted composite scores of all developmental domains in the unadjusted model. In the multivariable-adjusted liner regression model, we will adjust specific baseline test scores for each domain and any other related sociodemographic variables that are significantly different between the groups at baseline, significantly different between the children lost to follow up and the tested children, or significantly associated with developmental outcome measures, e.g., socioeconomic status, sex, mother’s education, HOME assessment result, etc. Five behavioral outcomes will be summed up as total scores and will be used in a similar analysis. Sensitivity and mediation analyses will also be conducted using a Structural Equation Model (SEM) [27] to explore the underlying mechanisms or processes influencing the outcomes.

The magnitudes and kinetics of the inflammatory markers will be compared at enrolment and over the follow-up period between DS cases and NDSD cases. Analyses for comparisons of dichotomous outcomes, such as fold increases/decreases in the markers from baseline, will be performed with the chi-square test or Fisher’s exact test if cell counts are sparse. For comparisons of the levels at a specific day between the two groups, a student’s *t*-test will be performed. MPO and LF data will be adjusted for breastfeeding. The data from the cases and their matched controls will be evaluated using paired *t*-tests. Linear regression analysis results will be compared between cases and controls adjusting for anthropometry and cognitive developmental changes, future diarrhea episodes, and antibiotic use in the follow-up period, and sociodemographic risk factors for inflammation.

For the RLDT evaluation at the rural primary healthcare facility, the RLDT results from the hospital staff will be compared with the results from the INSIGHT study staff (gold standard), analyzing sensitivity, specificity, and positive and negative predictive values. We will also use pairwise comparisons with Cohen’s kappa (measuring the agreement between binary outcomes +/− of tests without requiring a gold-standard).

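### The t-tests named for continuous outcomes do not fit the 1:2 matching of DS to NDSD, and for the inflammatory markers two tests that treat the matching differently are named without precedence

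*Protocol article*

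**What the plan says.** Protocol article, section 3.1, sets the design: "This is a matched set of cases (DS) and controls (NDSD) with two matched controls per case". The WD group is different: "The second comparison group is the WD group (1:1 matched with case". The planned numbers follow these ratios: "we will enroll 148 children each in the DS and WD groups and 296 in the NDSD group".

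Section 3.2 assigns the continuous outcomes as follows.

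- **Anthropometry:** "The Z scores of all anthropometric measurements of the cases and their matched controls at different time intervals will be compared using paired" *t*-tests. Linear regressions with jack-knife standard errors are added. The unit deleted in the jack-knife is not given.
- **Bayley and WPPSI scores:** the same techniques as for anthropometry.
- **Inflammatory markers, DS against NDSD:** "For comparisons of the levels at a specific day between the two groups", a Student's *t*-test. Shortly afterwards: "The data from the cases and their matched controls will be evaluated using paired" *t*-tests. Nothing says when each applies. Adjusted linear regression is also planned.

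For severity, symptoms and hospitalization at enrolment, section 3.2 names conditional logistic regression, which accommodates two controls per case.

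**The concern.** A paired *t*-test works on one difference per pair, and a DS case with two NDSD controls does not supply a single difference until someone decides how the controls are combined. The possible decisions do not have the same error rate or power. For the markers there is a further difficulty. Because a paired test is named separately, the Student's test must be the unpaired one. The two tests then make different assumptions about the same matched children: one uses the within-set correlation and the other ignores it.

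The growth, developmental and gut-health aims rest partly on these tests. If the choice is left until the data are in hand, the width of the confidence intervals depends on how the sentence is coded.

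**Working it through.** **Inputs.** From section 3.1: one DS to two NDSD; 148 DS and 296 NDSD enrolled; 123 sets required; 20% loss; within-set correlation 0.2, which the article gives for the binary exposure only. Assumptions made here: equal variances s², the same correlation ρ between any two members of a set, ρ = 0.2 borrowed for continuous outcomes with a range shown, and a two-sided 5% level.

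**The plan's own figure.** The article gives no power or precision figure for the *t*-tests. The 123 sets belong to the hospitalization calculation, and 123 × 1.2 = 147.6 gives the 148. A standard formula for matched case–control studies with the stated inputs gives 225 sets rather than 123. That is a separate matter; the point here needs only the 1:2 ratio.

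**True variance of the DS–NDSD difference**, using both controls in n complete sets: 1.5·s²(1−ρ)/n.

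**Each way of carrying out the named tests**

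1. *Case against the mean of its two controls.* The estimated variance matches the true one, so type I error is 0.05 (simulated 0.050 with 123 sets, ρ = 0.2).
2. *Case against one control.* Variance is 2·s²(1−ρ)/n. Efficiency is 1.5/2 = 0.75, the standard error is √(2/1.5) = 1.155 times as large, type I error stays at 0.05, and 148 of the 296 NDSD children are unused.
3. *Each case entered twice, 2n pairs taken as independent.* Assumed variance is 2·s²(1−ρ)/(2n) = s²(1−ρ)/n. True over assumed is 1.5, and ρ cancels. Type I error = 2[1 − Φ(1.96/√1.5)] = 2[1 − Φ(1.600)] = 0.11 (simulated 0.107 to 0.114 for ρ from 0 to 0.5).
4. *Unpaired Student's t-test.* Assumed variance is 1.5·s²/n, so the standard error is too large by 1/√(1−ρ). Type I error = 2[1 − Φ(1.96/√(1−ρ))]:

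| ρ | SE ratio | Type I error |
|---|---|---|
| 0 | 1.00 | 0.050 |
| 0.1 | 1.05 | 0.039 |
| 0.2 | 1.12 | 0.028 |
| 0.3 | 1.20 | 0.019 |
| 0.5 | 1.41 | 0.006 |

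**Power, for illustration only** (assumed difference 0.3 SD, 123 complete sets, ρ = 0.2, simulated): mean of controls 0.85, unpaired 0.80, one control 0.74.

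**Jack-knife** (unadjusted DS–NDSD difference, 123 sets, ρ = 0.2, simulated): type I error is 0.026 deleting one child at a time and 0.05 deleting one set at a time.

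**Effect of loss.** If each child is lost independently with probability 0.2 (assumption):

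- all three members remain: 0.8³ = 0.512, about 76 of 148 sets;
- the case and exactly one control remain: 0.8 × 2 × 0.8 × 0.2 = 0.256, about 38 sets;
- the case or both controls are gone: 1 − 0.512 − 0.256 = 0.232, about 34 sets.

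A set-mean paired test restricted to complete sets would use about half the sets at the end of follow-up. If sets with one control are added, their differences have variance 2·s²(1−ρ) beside 1.5·s²(1−ρ) for the rest, and the plain paired test weights them equally.

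**The case against.** The strongest reply is that a paired test of the case against the mean of its controls is standard, holds its level in complete sets and drops nobody, and that a journal article may leave such detail to the full protocol or analysis plan. This stands in part. A reader might infer that a paired *t*-test cannot be used with 1:2 sets, or that the analyst is forced either to discard half the controls or to report standard errors that are too small. The article supports neither. Nothing in it says that cases will be entered twice, so the 0.11 is a risk of one reading and not a planned error rate.

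Three other stronger readings also fail.

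- That growth and developmental scores are given conflicting *t*-tests: the Student's test is named for the markers only. For Z scores, a paired test for the crude comparison and regression for the adjusted one are complementary.
- That the regressions ignore the matching: for Z scores, jack-knife errors are stated, and they respect the sets if whole sets are deleted. The article does not say which unit is used.
- That everything is affected: the DS–WD comparison is 1:1 and suits a paired test, and hospitalization at enrolment is assigned conditional logistic regression. The first does not dispose of the point, because section 2.2 frames the comparisons as NDSD against DS and against WD.

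What the reply does not remove is that the article itself names an unpaired test for matched data and a second test beside it. That is a stated choice, not an omitted detail.

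**Conclusion.** The point holds in a limited form. For DS against NDSD, the named *t*-tests do not fit 1:2 sets without a further rule, and the marker analysis names a paired and an unpaired test with no order between them. The unpaired test is conservative: about 0.03 at correlation 0.2, from about 0.04 at 0.1 to 0.006 at 0.5, and no error at all at zero correlation. Entering cases twice would give about 0.11 at any correlation; using one control keeps 75% of the information. Set-mean pairing is valid for complete sets, but only about 51% of sets would be complete at the end of follow-up under independent 20% loss.

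These sizes rest on equal variances and exchangeable correlation. The value 0.2 is borrowed from the binary outcome, and the 0.3 SD difference is illustrative. The hospitalization hypothesis on which the study is sized is untouched, so this should be corrected before analysis but does not threaten the main comparison.

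**What to change.** For DS–NDSD continuous outcomes, replace the paired and unpaired *t*-tests by one method that respects the matched set. A linear mixed model with random intercepts for matched set and child uses both controls and incomplete sets; matched-set fixed effects or set-clustered standard errors are acceptable alternatives.

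Two details should be written in:

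- Estimate enrolment contrasts with the enrolment value as an outcome. Adjust for the enrolment value only in the change analyses where the plan already does so; a single model with it as a covariate throughout could not estimate the planned enrolment comparisons.
- Where jack-knife standard errors are kept, delete one matched set at a time.

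The cost is analysis wording and modest programming. No new data or change in enrolment is needed.

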It may be hypothesized that NDSD cases, if identified quickly, should be treated with antibiotics or other therapeutics to improve the survival and long-term developmental potential of the children. Shigellosis cannot be distinguished reliably from other causes of bloody diarrhea or other causes of watery diarrhea based on clinical features alone. Documenting NDSD infections and rationally guiding treatment will require a point-of-care (POC) test for Shigella so that the treatment can be initiated promptly. Chakraborty et al. previously developed and successfully evaluated, in Asian and African countries, a simple molecular diagnostic test for Shigella: the Rapid LAMP-based Diagnostic Test (RLDT), which detects Shigella from a fecal sample within one hour and thus has the potential to be used for the rapid detection and treatment of NDSD [17,18,19,20].

We are conducting a prospective longitudinal case–control study (INSIGHT) in Mirzapur, Tangail, Bangladesh, to determine if there is a need to change the current guidelines on shigellosis treatment for improving the survival and development of children with this condition. We will determine the impact of NDSD on immediate and long-term (1-year) morbidity and development in children under 5 years old compared with DS and non-Shigella watery diarrhea (WD). We will also assess the potential for implementation of the RLDT for Shigella in a rural primary healthcare government facility in Bangladesh.

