### 2.2. Aims

The objectives of this study are to (1) determine the morbidity, risk of hospitalization, and mortality associated with NDSD cases; (2) study the impact of NDSD on the nutritional status and cognitive development of children; (3) understand the impact of NDSD on gut barrier function, systemic inflammation, and gut inflammation in children; (4) determine the Shigella isolates’ resistance to commonly used antibiotics using disk diffusion tests and E-strips; and (4) evaluate if the RLDT could be applicable for the detection and treatment of shigellosis cases in the low-resource clinical settings of a rural primary healthcare facility. The data from aims (1) to (3) will be compared between the NDSD group and the other two groups, DS and WD.

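### The adjusted growth and inflammatory-marker regressions condition on events after the index episode, so they do not estimate the total impact of NDSD named in aims 2 and 3

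*Protocol article*

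**What the plan says.** The Introduction of the protocol article states the goal: "We will determine the impact of NDSD on immediate and long-term (1-year) morbidity and development in children under 5 years old". In section 2.2, aim 2 is to "study the impact of NDSD on the nutritional status and cognitive development of children", and aim 3 asks the same for gut barrier function and inflammation. NDSD is to be compared with DS and WD, so the exposure is the type of index episode.

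Section 3.2 then gives three adjusted linear models:

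- **Growth.** Besides the enrolment Z score, follow-up duration and sociodemographic covariates, the model adjusts for "antibiotic use, future diarrhea episodes, and any hospitalization in the follow-up period, using jack-knife estimates of standard error".
- **Inflammatory markers.** The model is fitted "adjusting for anthropometry and cognitive developmental changes, future diarrhea episodes, and antibiotic use in the follow-up period", together with sociodemographic risk factors.
- **Development (Bayley, WPPSI).** Here "we will adjust specific baseline test scores for each domain and any other related sociodemographic variables", for example socioeconomic status, sex, maternal education and HOME.

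Three further statements in section 3.2 matter. "The impact of the initial shigellosis or WD episode on the future morbidity, hospitalization, and mortality of the children" is itself to be analysed. Paired t-tests without covariates are planned for growth and for the markers. And, in the development paragraph, "mediation analyses will also be conducted using a Structural Equation Model (SEM"). No adjusted growth or marker model limited to baseline covariates is described.

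**The concern.** A covariate removes confounding if it is a cause, or a stand-in for a cause, of both group and outcome. A variable that the group itself influences does something else. If it lies between the index episode and growth, holding it fixed takes out the part of the effect that passes through it. If it also shares unmeasured causes with the outcome, holding it fixed links group to those causes and adds bias of unknown sign.

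The marker model has a further difficulty. Growth and cognitive change are, on the article's own account, possible results of inflammation. Adjusting a marker for its own consequences cannot be confounder control.

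At stake is the meaning of the adjusted results for aims 2 and 3. The Discussion says that the study is to show whether rehydration and zinc without antibiotics is adequate for NDSD. A reader would take the adjusted group coefficient as the impact of NDSD, which it is not.

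**Working it through.** The documents give no figure to reproduce. The check sets the covariate lists against what the article says elsewhere, then illustrates the consequence.

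**Step 1: the lists side by side (section 3.2)**

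| Post-index variable | Growth model | Marker model | Bayley/WPPSI model | Its role elsewhere in the article |
|---|---|---|---|---|
| Later diarrhea | covariate | covariate | not listed | future morbidity analysed as an impact of the index episode (3.2) |
| Later hospitalization | covariate | not listed | not listed | analysed as an impact of the index episode (3.2) |
| Antibiotic use | covariate | covariate | not listed | to be recorded and considered (3.2); not an aim 1 outcome |
| Growth change | outcome | covariate | not listed | outcome under aim 2; malnutrition is a possible result of the inflammation (Introduction) |
| Cognitive change | not listed | covariate | outcome | outcome under aim 2; impairment is a possible result of the inflammation (Introduction) |

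I read antibiotic use in the growth list as use during follow-up, in line with the earlier sentence in section 3.2. The table shows the same events serving as consequences of the exposure in one analysis and as adjustment factors in another.

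**Step 2: what adjustment does to the coefficient (illustration)**

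All inputs are assumptions: total effect -0.30; each unit of a later event lowers the outcome by b = 0.3; error SD 1 for event and outcome. Let s be the mediated share and a the group effect on the event.

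- Mediated part: a × b = 0.30s, so a = s. Direct part: -0.30(1 - s).
- Case A, no shared cause: adjusted coefficient = -0.30(1 - s).
- Case B, an unmeasured cause (variance 1) raises the event by 0.5 and lowers the outcome by 0.5. Given group and event, its expected value moves by 0.5/(0.5² + 1) = 0.4 per unit of event not explained by group. The group coefficient picks up 0.5 × 0.4 × a = 0.2s, giving -0.30(1 - s) + 0.2s.
- Case C, the same cause moves event and outcome in the same direction: -0.30(1 - s) - 0.2s.

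| s | Without the event | Case A | Case B | Case C |
|---|---|---|---|---|
| 0% | -0.30 | -0.30 | -0.30 | -0.30 |
| 25% | -0.30 | -0.225 | -0.175 | -0.275 |
| 50% | -0.30 | -0.15 | -0.05 | -0.25 |
| 75% | -0.30 | -0.075 | +0.075 | -0.225 |
| 100% | -0.30 | 0.00 | +0.20 | -0.20 |

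A simulation with 400,000 children agrees for A (-0.298, -0.227, -0.153, -0.071, 0.000) and B (-0.305, -0.171, -0.055, +0.073, +0.197). The model without the event gave -0.298 to -0.305 throughout. Case C is from the formula only. Relative to the direct effect, the shared cause biases in either direction; in case B the sign of the estimate reverses.

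**Step 3: what attenuation would mean at this size of study**

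Take 148 DS and 296 NDSD children (section 3.1), outcome SD 1, two-sided 5%, ignoring matching and dropout. The standard error is √(1/148 + 1/296) = 0.1007. Power is Φ(difference/0.1007 - 1.96): 85% for 0.30, 61% for 0.225 and 32% for 0.15.

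**Step 4: the marker model**

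Growth and cognitive change lie after inflammation, not between the index episode and inflammation, so the mediated-share formula does not apply. Group and marker can both affect growth. Holding growth fixed therefore induces an association between them, with no predictable sign.

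**The case against.** The strongest replies, and what stands of each:

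- **Estimates without this adjustment are planned.** True. The paired t-tests on Z scores and markers avoid it, and later morbidity, hospitalization and mortality are analysed in their own right, so harm through recurrent illness would show there. But the t-tests control confounding only through matching, and every adjusted growth or marker estimate that the article describes has the problem.
- **A mediation analysis is planned.** The SEM is placed in the development paragraph as an exploration of mechanisms. It does not change what the growth and marker regressions estimate.
- **Later diarrhea or antibiotics may stand in for household exposure or care-seeking.** This is fair, and for antibiotics the causal role is open. The day 3 sociodemographic, sanitation and hygiene questionnaire and HOME (Table 1) can address household background without conditioning on later events.
- **An article condenses the protocol.** That covers omissions. These covariates are stated.

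A reader might also infer more than the text supports:

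- That the development models are affected, because "The same analytic techniques will be used for evaluating the data from the Bayley and WPPSI scales". That sentence ends by referring to the unadjusted model, and the adjusted model lists only baseline scores and sociodemographic variables.
- That the adjustment erases the NDSD effect, or always favors current care. It removes only the mediated part, which may be none, and shared causes can push the estimate either way.
- That antibiotic use is an aim 1 outcome. Aim 1 covers morbidity, hospitalization and mortality only.
- That the hypothesis behind the sample size is compromised. Hospitalization at enrolment is analysed by conditional logistic regression, which this point does not touch.

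**Conclusion.** The point holds for two models. The adjusted growth regression and the adjusted marker regression condition on events that the article elsewhere treats as consequences of the index episode or of the inflammation. Their group coefficients omit whatever part of the NDSD effect runs through those events and may carry collider bias in either direction. They therefore do not estimate the total impact named in aims 2 and 3. Adjusting the markers for growth and cognitive change is the least defensible choice.

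The size is unknown. The documents give no expected effect, mediated share or strength of shared causes, so the figures above show only what could happen. If nothing is mediated and growth and cognitive change are not affected by group or marker, nothing is lost. The conclusion about what is being estimated does not depend on those figures; it rests on the order in time and on the article's own description of these variables as outcomes.

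**What to change.** In section 3.2:

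1. Define the main adjusted growth and marker models with pre-exposure or baseline covariates only: matching factors, age, sex, sociodemographic variables, HOME, and breastfeeding for MPO and LF. HOME is taken at the first visit after enrolment and enters as a background measure. Keep duration of follow-up, and include the enrolment value of the outcome for change analyses. Enrolment markers are measured during the index illness, so compare enrolment levels themselves without that term.
2. Take later diarrhea, hospitalization and antibiotic use out of these main models. Report models that include them only as labelled mediation or sensitivity analyses, and extend the SEM to growth and markers for this purpose.
3. Drop growth change and cognitive change as covariates for the markers.
4. State that the adjusted Bayley/WPPSI model carries none of the later-event covariates, so that the reference to the same techniques cannot be misread.

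No new data are needed. The cost is a wording change in section 3.2 and a little more analysis, chiefly extending the SEM beyond development.
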